### **7) Efficacy**

Efficacy analysis will be performed for ITT (*Intention to treat*) group, and supplemental

analysis will be performed for PP (*Per protocol*) and *As treated* group. The primary endpoint will be concluded as 'significantly different' if both ITT and PP analyses confirm the significance of difference.

ITT group includes all study population. PP group is constituted from the ITT group after excluding the patients with major violation of the study protocol.

The null hypothesis is that the IMT of Y-composite group is comparable to that of aortocoronary group measured by IVUS on 1-year angiogram. The result for the primary endpoint will be presented with 95% two-sided confidence interval for mean difference between groups. The superiority test will be performed using a t-test which compared mean difference between groups under the two-sided significance level of 0.05.

For analysis of 1-year clinical outcomes, including all-cause mortality, cardiac death, target vessel revascularization, and reintervention, events will be counted at postoperative 1 year, and comparisons between the 2 groups will be made using the chi-square test and Fisher's exact test. A P value of  $< .050$  will be considered statistically significant.

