### **3) Sample size calculation**

Based on previous studies, the reference IMT was estimated;  $0.31 \pm 0.12$  mm for the Y-composite configuration and  $0.43 \pm 0.09$  mm for the aortocoronary configuration. The study was designed to have 90% power to detect a significant difference in IMT between the 2 groups with a 2-sided type I error of 5.0%. Based on this power calculation, 17 patients were needed in each group. Allowing for a 30% dropout rate during the 1-year follow-up, recruitment of 50 patients (25 patients in each group) was determined to be necessary.

(1) Level of significance ( $\alpha$ ) = 0.05

(2) Type II error ( $\beta$ ) = 0.10, power of the test = 90%

(3) Drop out rate = 30%

(4) Two-tailed test

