### **5) Criteria for suspension and dropout**

Patients who decline to participate in the trial are suspended or drop-out

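### The primary conclusion requires significance in both ITT and PP, although PP is labelled supplemental and the 90% power was calculated for a single test

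*Protocol*

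**What the plan says.** Protocol section 10, 7) Efficacy, assigns the efficacy analysis to the ITT population and calls the PP and as-treated analyses supplemental. The next sentence sets the decision rule: the primary endpoint is declared different "if both ITT and PP analyses confirm the significance of difference". On the sets themselves: "PP group is constituted from the ITT group after excluding the patients with major violation of the study protocol". No expected number of exclusions is given. The same section specifies a superiority t-test at the two-sided 0.05 level, with a 95% confidence interval for the mean difference.

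Section 9, 3) Sample size calculation, sizes one comparison at a two-sided alpha of 0.05: "The study was designed to have 90% power to detect a significant difference in IMT between the 2 groups". It concludes that "17 patients were needed in each group". The only inflation is for loss to follow-up, "Allowing for a 30% dropout rate during the 1-year follow-up", which brings the total to 50 (25 per group). Section 10, 5) Criteria for suspension and dropout, describes dropouts as refusals and does not mention protocol violators: "Patients who decline to participate in the trial are suspended or drop-out".

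**The concern.** Two adjacent sentences disagree. An analysis whose non-significance can block the primary conclusion is a co-primary requirement, whatever it is called.

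The rule also does not suit the objective. In a superiority trial the ITT comparison is the one protected by randomisation. The PP set depends on judgements about major violations made after randomisation. Under the rule as written, a significant randomised comparison can be set aside because a selected subset, with fewer patients, did not also reach 0.05.

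Finally, the power statement and the decision rule describe different things. The 90% refers to one t-test in one population, but the trial succeeds only if two nested tests both succeed. Two things are at stake: whether the trial can declare a difference that its ITT analysis supports, and whether readers are told the correct probability of that happening.

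**Working it through.** **Inputs from the protocol (section 9, 3).** Mean IMT 0.31 mm (SD 0.12) for Y-composite and 0.43 mm (SD 0.09) for aortocoronary, a difference of 0.12 mm; two-sided alpha 0.05; power 90%; dropout 30%; allocation 1:1.

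**Step 1: reproduce the plan's figures.** With the protocol's formula,

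n = (1.960 + 1.282)² × (0.12² + 0.09²) / 0.12² = 10.51 × 0.0225 / 0.0144 = 16.42, rounded up to 17 per group.

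17 / 0.70 = 24.3, rounded up to 25 per group, 50 in total. Both stated figures reproduce, for a single test.

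**Step 2: power of the ITT test alone at 17 per arm.** The standardised difference is 0.12 / √(0.0225/17) = 0.12 / 0.0364 = 3.30. The normal approximation gives Φ(3.30 − 1.96) = 0.910. The noncentral t with 32 degrees of freedom gives 0.892. The stated 90% is therefore sound if ITT alone decides.

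**Step 3: power of the two-set rule.** A trial counts as positive only if both tests are significant, so joint power cannot exceed ITT power. To size the gap, 100,000 trials per scenario were simulated with a pooled t-test at two-sided 0.05 and the PP set nested in the ITT set. *Assumptions not in the protocol:* the number of PP exclusions, that they are balanced between arms and random, and that the effect is the same in both sets.

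| Evaluable per arm (ITT) | PP exclusions per arm | ITT power | Both significant |
|---|---|---|---|
| 17 | 0 | 0.892 | 0.892 |
| 17 | 1 | 0.892 | 0.860 |
| 17 | 2 | 0.892 | 0.836 |
| 17 | 3 | 0.891 | 0.806 |
| 17 | 4 | 0.893 | 0.777 |
| 20 | 1 | 0.936 | 0.916 |
| 20 | 2 | 0.936 | 0.901 |
| 20 | 3 | 0.937 | 0.883 |
| 25 | 1 | 0.975 | 0.967 |
| 25 | 4 | 0.974 | 0.944 |
| 25 | 6 | 0.976 | 0.922 |
| 25 | 8 | 0.975 | 0.888 |

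**Step 4: discordant trials.** At 17 per arm with 2 exclusions per arm, 0.892 − 0.836 = 0.056. About 6% of trials would be significant in ITT but not declared different.

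**Step 5: type I error.** With no true difference, both tests were significant in about 3.4% of trials (17 per arm, 2 exclusions) and 2.8% (17 per arm, 4 exclusions), against about 5% for ITT alone.

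**The case against.** The strongest reply is that the loss depends on two numbers, actual dropout and PP exclusions. The protocol plans for the first at 30% and gives none for the second. Taking 17 evaluable per arm and then removing more patients puts one pessimistic assumption on another. This stands. A reader might infer that the 90% fails as soon as any patient leaves the PP set, but the table does not support that: at 20 per arm joint power is about 90% with 2 exclusions per arm, and at 25 per arm it is 92% with 6. Even 30% off 25 leaves 17.5; at 18 per arm a separate simulation (40,000 trials) gave 88%, 86% and 83% for 1, 2 and 3 exclusions. If the whole 30% allowance were used up by PP exclusions (25 in ITT, 17 in PP), joint power would be 0.888, close to the single-test value. However, the protocol describes that allowance as loss during follow-up, so this is a bound and not the stated plan.

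It is also fair that the design may keep exclusions few. Randomisation takes place during surgery, once the conduits are harvested and either strategy is judged feasible (section 10, Operative strategies and Randomization process). A patient without a 1-year IVUS has no IMT and, in a complete-case t-test, would be absent from both sets. ITT and PP may then nearly coincide.

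Three stronger readings are not supported:

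- **Inflated false-positive risk.** The rule is conservative, as Step 5 shows.
- **A contradiction with the promised confidence interval.** The interval for the mean difference is still reported. Withholding a label under a stricter pre-stated rule does not change it.
- **A PP definition that is too loose.** The list of major violations is commonly left to the SAP, which is not at hand. The definition matters here only because PP is made decisive.

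None of this removes the conflict between the supplemental label and the decision rule, or the mismatch between that rule and a sample size for one test.

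**Conclusion.** The point holds in this form. The protocol labels PP supplemental but makes its significance a condition of the primary conclusion in a two-sided superiority trial, and the stated 90% is the power of one test, not of that rule. This is true whatever the number of exclusions.

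The size of the loss is conditional. At the planned 17 evaluable per arm it is roughly 3 to 9 percentage points below the ITT t-test power of 89% for 1 to 3 exclusions per arm (89.2 − 86.0 = 3.2; 89.2 − 80.6 = 8.6). It is zero if the two sets coincide, and joint power can remain at or above 90% if dropout is well below 30%. About 1 to 2 points of the distance from the protocol's figure come from using the t-test in place of the normal formula (91.0 − 89.2 = 1.8), not from the rule. The results rest on the planning means and SDs and on the Step 3 assumptions. A larger effect in PP would lessen the loss and a smaller one would worsen it.

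**What to change.** In section 10, 7) Efficacy, replace the two-set sentence with wording such as: *The primary conclusion rests on the two-sided t-test in the ITT population at the 0.05 level; the PP and as-treated analyses are supportive and do not alter it.* This agrees with the supplemental label and with the single test for which section 9 sized the trial.

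The cost is one sentence: no additional patients or data, and PP is still reported. The change should be dated before IMT is compared between the groups.

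If the two-set rule is kept on purpose, remove the supplemental label, state the assumed number of PP exclusions per arm, and state the resulting joint power in place of 90%. The percentages above should not simply be copied in, because they depend on exclusion counts assumed here; the investigators need to supply their own.

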#### Operative strategies and Randomization process

Surgeries will be performed under standard median sternotomy, and off-pump CABG (OPCAB) will be the preferred grafting strategy during the study period. The in situ LITA will be

harvested using the skeletonization technique. The SV will be simultaneously harvested, preferentially from the lower leg, using a NT technique that retains perivascular soft tissue as previously described. Randomization will be performed after the conduits are harvested without injury and it is confirmed that the intraoperative findings indicate that either of the grafting strategies are feasible. Web-based block randomization will be performed using randomly determined block sizes of 4 and 6. After randomization, the procedures will be performed according to the assigned grafting strategy. In the patients assigned to the Composite group, the Y-composite graft is constructed first by anastomosis of the distal end of the SV graft to the side of the LITA, and anastomosis of the LITA to the LAD territory is performed whenever necessary. The SV is then anastomosed to the diagonal branch, to the vessels in the left circumflex coronary artery(LCX) territory, and then to the vessels in the right coronary artery(RCA) territory as needed using a sequential anastomotic technique. In the patients assigned to the Aorta group, the SV is first anastomosed to the ascending aorta using the Heartstring III Proximal Seal System (MAQUET Holding B.V. & Co. KG, Rastatt, Germany). The LITA is then anastomosed to the target vessel in the LAD territory. Finally, the SV is anastomosed sequentially to the diagonal branch, to the vessels in the LCX territory and then to the vessels in the RCA territory as needed using a sequential anastomotic technique.

※ Randomization : Patients who meet the inclusion criteria and the exclusion criteria are randomly assigned to 1 of the 2 configurations in a 1:1 manner. Randomization is performed with a web-based block randomization method (<https://mrcc.snuh.org/>) with randomly determined block sizes of 4 and 6.

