### **Histologic evaluation of the saphenous vein**

Immediately after harvesting, the distal end of the SV, approximately 2mm in length, will be sampled and preserved as formalin-fixed paraffin-embedded tissue for histologic evaluation. The histologic evaluation is designed to compare the intima-media thickness (IMT) of the SV in the 2 groups as a baseline value of the IMT and as an indicator of the quality of the SV. The specimen will be divided into 3 sections perpendicular to the vessel lumen. Histologic evaluation will be performed using hematoxylin and eosin staining and Masson's trichrome staining. The IMT will be measured in 4 directions for each section, and the values obtained for the 3 sections will be averaged.

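### A histologic baseline IMT is collected before randomised grafting but left out of the primary t-test; a prespecified adjusted analysis would probably cost little and would help if the correlation with 1-year IVUS IMT exceeds about 0.2

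*Protocol*

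**What the plan says.** Three parts of the protocol's Methods (section 10) bear on this point.

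- **Histologic evaluation of the saphenous vein.** A piece of about 2 mm is taken from the distal end of the vein immediately after harvest. Its IMT is measured in four directions on each of three sections and averaged. The stated purpose is to compare the two groups, with the measurement serving "as a baseline value of the IMT and as an indicator of the quality of the SV".
- **Operative strategies and Randomization process.** "Randomization will be performed after the conduits are harvested without injury", and once either grafting strategy is confirmed to be feasible. Grafting follows allocation.
- **7) Efficacy.** The primary endpoint, 1-year IMT by IVUS, is reported as a mean difference with a two-sided 95% confidence interval. The test is also fixed: "The superiority test will be performed using a t-test which compared mean difference between groups under the two-sided significance level of 0.05".

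The protocol names no covariate for the primary endpoint.

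**The concern.** The tissue is taken before the vein is grafted in either configuration, so allocation cannot change it, even if the slides are read later. Its IMT is therefore a legitimate baseline covariate. The protocol itself regards it as informative about the vein whose IMT is the endpoint.

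Comparing it between arms is of limited use. After proper randomisation such a comparison can show only chance imbalance, and the protocol gives no way to act on one. Adding an adjustment after seeing an imbalance would be data-driven, so the choice has to be made in advance.

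Two things are at stake: the width of the confidence interval, and how far a chance difference in vein quality can move the estimate in a trial of this size. This is not simply a detail left to a statistical analysis plan, because the protocol itself names the primary test.

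**Working it through.** **Inputs from the protocol (Sample size calculation).** IMT 0.31 mm (SD 0.12) for Y-composite and 0.43 mm (SD 0.09) for aortocoronary, a difference of 0.12 mm; two-sided alpha 0.05; power 90%; 17 evaluable per arm; 30% dropout; 25 recruited per arm.

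**Input not in the protocol.** The correlation r between baseline histologic IMT and 1-year IVUS IMT. It is varied below as an assumption.

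**Step 1: reproduce the plan's figure.** The protocol's formula gives

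n = (1.960 + 1.282)² × (0.12² + 0.09²) / 0.12² = 10.507 × 0.0225 / 0.0144 = 16.42, rounded up to 17.

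Then 17 / 0.70 = 24.3, rounded up to 25 per arm, 50 in total. Both figures match the protocol ("Based on this power calculation, 17 patients were needed in each group").

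**Step 2: power of the t-test as planned.** The common SD is s = sqrt((0.12² + 0.09²)/2) = 0.106. At 17 per arm SE = 0.106 × sqrt(2/17) = 0.0364, and 0.12/0.0364 = 3.30. The noncentral t with 32 degrees of freedom gives power 89.2% (89.1% by Welch) and a 95% CI half-width of 0.0741 mm. At 25 per arm the figures are 97.5% and 0.0603 mm.

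**Step 3: adjust for baseline.** The residual variance is multiplied by (1 − r²), one degree of freedom is lost, and the expected penalty for chance baseline imbalance is included:

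SE(adjusted) = s × sqrt(2/n) × sqrt(1 − r²) × sqrt(1 + 1/(2n − 4)), with 2n − 3 degrees of freedom.

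Example, n = 17 and r = 0.3: 0.0364 × 0.954 × 1.017 = 0.0353.

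| Analysis | Power, 17/arm | CI width vs t-test, 17/arm | Power, 25/arm | CI width vs t-test, 25/arm |
|---|---|---|---|---|
| t-test | 89.2% | 1.000 | 97.5% | 1.000 |
| Adjusted, r = 0 | 88.2% | 1.018 | 97.2% | 1.011 |
| Adjusted, r = 0.2 | 89.4% | 0.997 | 97.7% | 0.991 |
| Adjusted, r = 0.3 | 90.9% | 0.971 | 98.2% | 0.965 |
| Adjusted, r = 0.4 | 92.9% | 0.933 | 98.8% | 0.927 |
| Adjusted, r = 0.5 | 95.2% | 0.881 | 99.4% | 0.876 |

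The CI widths break even at r of about 0.19 with 17 per arm and about 0.15 with 25 per arm.

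**Step 4: chance imbalance.** At 17 per arm the standardised baseline difference has standard error sqrt(2/17) = 0.34. An imbalance of at least 0.5 SD then has |z| of at least 0.5/0.343 = 1.46, which occurs in about 14% of trials. An imbalance of exactly 0.5 SD shifts the unadjusted difference by 0.5 × r × 0.106 mm:

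- r = 0.3: 0.016 mm, 13% of the 0.12 mm planning difference.
- r = 0.5: 0.027 mm, 22% of it.

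**The case against.** The strongest reply is that nothing is broken. A two-sided t-test with a 95% confidence interval is a valid analysis of a randomised comparison. It matches the stated hypotheses and the sample-size formula, and its interval already allows for chance imbalance. All of that stands. A reader might infer that the primary test or the sample size is wrong; the protocol supports neither reading.

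A second reply is that the gain rests on a correlation nobody has stated. A reader might infer that the t-test certainly gives up precision. The protocol does not support that, and it offers reasons for caution. The baseline is one formalin-fixed piece of about 2 mm from the end of the vein. The endpoint is IVUS in the living patient a year later, measured every millimetre along several centimetres of graft. If the correlation is below about 0.2, adjustment gains nothing. This reply stands too, and it makes the point conditional.

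A third reply is that 17 per arm is what is left after the full dropout allowance. With better retention unadjusted power is already high: 93.6% at 20 per arm and 97.5% at 25. That is correct, and it moves the benefit from power to precision and control of imbalance. Nor is the gap between 89.2% and the planned 90% an argument in itself. It comes from using the normal approximation, and adjustment closes it only at a correlation somewhere between 0.2 and 0.3.

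Finally, a reader might infer that the protocol plans a significance test of baseline IMT. It speaks of comparing the groups and names no such test, so there is none to remove.

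What remains is an imbalance in cost and benefit. The measurement is already planned, the worst expected loss is about 1 point of power, and the possible gain is several times larger.

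**Conclusion.** The point holds as a conditional efficiency improvement. The protocol collects a baseline value of the endpoint quantity, on tissue that allocation cannot affect, and fixes a primary analysis that does not use it. Neither the validity of the t-test nor the sample size of 50 is in question.

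At 17 evaluable per arm, adjustment changes power by −1.0, +0.2, +1.7, +3.7 and +6.0 points at correlations 0, 0.2, 0.3, 0.4 and 0.5 (for example 95.2 − 89.2 = 6.0). The CI ranges from about 2% wider at 0 to about 12% narrower at 0.5. At 25 per arm the power gain is small, and the CI is about 4% narrower at 0.3 and 12% narrower at 0.5.

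These figures assume the protocol's planning means and SDs, a linear relation with the same slope in both arms, and a correlation that has to be assumed.

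**What to change.** In 7) Efficacy, prespecify the primary analysis as a linear model of 1-year IVUS IMT on randomised arm and baseline histologic IMT, reporting the adjusted mean difference with its 95% CI and two-sided p-value. Keep the t-test as a sensitivity analysis. Use the same model in the ITT and PP sets, because the protocol requires both to be significant.

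Replace a missing histology value by the overall mean across both arms, so that no patient is lost from the model. Describe baseline IMT by arm. Do not use a change from baseline: histology and IVUS are different methods, and their difference has no clear meaning.

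The cost is a sentence or two in the protocol, one degree of freedom and, if the baseline proves uninformative, about 1 point of power at 17 per arm. It needs no extra patients or measurements. The change should be made before any outcome data are seen.

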## **8) Schedules**

- ① Study planning : March 1, 2021 – June 30, 2021
- ② Enrollment : July 8, 2021 – October 26, 2022
- ③ Data analysis and reporting : January 1, 2023 – December 31, 2023

### **2) Data and Safety Monitoring List**

Operative mortality, low cardiac output, bleeding reoperation, perioperative myocardial infarction, perioperative stroke, acute kidney injury, respiratory complications, postoperative atrial fibrillation, and mediastinitis

### **3) Data and Safety Monitoring Periods**

Safety outcomes will be monitored every 6 months.

#### **4) Reporting drug adverse events, non-compliance, or unpredicted events**

If any drug adverse event, non-compliance, or unpredicted event occurs, they must be reported within 15 working days from the date of recognition.

#### **5) Withdrawal of the trial**

If critical adverse events or complications associated with the trial occur and it is impossible to keep the trial going on, the trial will be withdrawn.

### **12. Ethics**

The Investigators and all parties involved will conduct this study in adherence to the ethical principles based on Declaration of Helsinki, GCP, ICH guidelines and the applicable national and local laws and regulatory requirements. Relevant study documentation will be submitted to Ethics Committees of participating centers, according to local/national requirements, for review. Written approval of the study must be obtained locally before the study commences at each participating center. Once protocol amendments or consent form modifications are approved and implemented at the lead center, updated documents will be provided to participating centers. On completion of the study, the regulatory authorities will be notified that the study has ended.

